# V. Hypothesis

Three doses of artesunate combined with SP or amodiaquine, and Lapdap used alone will be equally as effective at preventing malaria in young Senegalese children when used for sIPT as a regimen of SP combined with one dose of artesunate and less likely to select for resistant parasites

Two major endpoints will be considered in this study (i) the incidence of clinical malaria in children receiving one of these four interventions, (ii) the prevalence of parasites carrying genotypes associated with resistance following sIPT at the end of the transmission season.

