2.2. Exclusion criteria

Reasons for exclusion will include any of the following:

Any conditions causing an inability to take or retain oral medication.

Any chronic illnesses or severe conditions such as tuberculosis, epilepsy, obvious mental retardation or failure to thrive.

Severe congenital diseases such as heart malformations

Intake of an anti-malarial other than chloroquine within the previous two weeks

Known allergy to any of the antimalarial drugs used in the trial.

1. Study design

We will use an open label randomised trial comparing the following regimens:

- Artesunate one day plus SP

- Artesunate given for three days plus SP

- Artesunate plus Amodiaquine both given for three days

- Lapdap for three days

One of these combinations will be randomly allocated to all participants and given three times in early September, early October and early November 2004.

1. Sample size calculations

The trial is powered as an ‘equivalence’ or ‘negative’ trial, with the outcome being the cumulative incidence of malaria, ie the proportion of children having at least one episode of malaria during the course of the study. AS3+SP is the comparator and is expected to have cumulative incidence of 20%, and we aim to show that this is no more than 30% in the other three arms. To allow for three comparisons — AS3+SP compared with each of the other three arms — we set the significance level to 5/3% (≈0.0167%), one-sided. With 80% power, we need 336 children per arm (Jones, Jarvis et al. 1996). We expect no more than 20% to be lost to follow-up, which raises this to 420 per arm, or 1680 in total.

For the secondary drug resistance endpoint, this implies 336×0.2=67 cases on AS3+SP. To be conservative, we assume the same number on the other arms (if they turn out to be less effective than AS3+SP, this will only increase the power for this secondary endpoint). Among these cases, based on our previous study, we expect the prevalence of *dhfr* mutations at codons 108, 59 and 51 to be 90% in the AS1+SP arm. The 67 cases per arm then give us 77% power to detect a difference of 20% (ie 70% prevalence) in the other arms, with a significance level of 5% (two-sided, (Fleiss 1981)).

1. Enrolment procedure and follow-up

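### Splitting the level equally over three non-inferiority comparisons gives up power that a Holm step-down test at the same 5% family level would keep

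*Protocol*

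**What the plan says.** The sample size section of the Protocol (item 4 of section VI) treats the trial as an equivalence trial on the proportion of children with at least one malaria episode. AS3+SP is the comparator, with an expected cumulative incidence of 20%. Of that incidence the protocol says: "we aim to show that this is no more than 30% in the other three arms".

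The multiplicity rule starts "To allow for three comparisons — AS3+SP compared with each of the other three arms", and its level is given thus: "we set the significance level to 5/3% (≈0.0167%), one-sided". The bracketed percentage is a slip for 0.0167, since 5/3% is 1.67%.

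The size follows: "With 80% power, we need 336 children per arm", and then "We expect no more than 20% to be lost to follow-up, which raises this to 420 per arm, or 1680 in total".

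The section does not say whether the 80% applies to one comparison or to all three. It gives no power for all three and names no step-down procedure. Section 13.3, on end-points and analysis, describes rate ratios, Kaplan-Meier curves and a log-rank test. It gives no rule for testing the three comparisons.

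**The concern.** An equal split tests every comparison at one third of the family level, whatever the other two show. A step-down procedure begins at that same third but relaxes the level once a comparison has succeeded, and the family-wise error is still held. An equal split therefore gives up power with no gain in family-wise error control.

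The purpose of the trial is to choose among regimens. If a regimen truly matches the comparator, a needlessly strict test may leave it as not shown, and it could be passed over for that reason. A reader of the sample size section also cannot tell how likely the trial is to place all three arms within the margin.

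**Working it through.** **Inputs** (sample size section): incidence 20% in the comparator; margin 30% − 20% = 10 points; one-sided level 5/3% = 1.67% per comparison, so 5% for the family; 336 evaluable per arm; one shared comparator. The true incidence in the other arms is an assumption: 20% unless stated otherwise.

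**1. The plan's own figure.** For one non-inferiority comparison with unpooled variance,

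n = [0.2×0.8 + 0.2×0.8] × (z_α + 0.8416)² / 0.1² = 32 × (z_α + 0.8416)².

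- One-sided 1.67%, as stated: z = 2.128, n = 32 × 2.9697² = 282.2, so 283.
- One-sided 0.83% (5/3% taken as two-sided): z = 2.394, n = 32 × 3.2356² = 335.01, so 336.

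The printed 336 is thus reproduced by a formula for a single comparison, but at a stricter level than the one stated. For loss to follow-up, 336/0.8 = 420, and 4 × 420 = 1680, as printed.

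**2. Power per comparison at the stated level.** The standardised margin is 0.1/√(0.32/336) = 3.240. Power is Φ(3.240 − 2.128) = Φ(1.112) = 86.7%.

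**3. Power for all three, equal split.** The three test statistics share the comparator arm, so with equal arms their correlation is 0.5. The trivariate normal probability that all three succeed is 72.2%. Binomial simulation (four arms of 336, unpooled Wald test, at least 400,000 trials) gives 71.0%. The chance that at least one arm is not shown is therefore about 29%.

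**4. Holm.** Order the three one-sided p-values. Compare the smallest with α/3, the next with α/2 and the largest with α, stopping at the first failure; here α = 5%. The first threshold equals the fixed one and the others are larger, so Holm rejects everything that the equal split rejects.

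| True incidence in the other arms | Power | Fixed 5/3% | Holm, family 5% |
|---|---|---|---|
| 20%, 20%, 20% | each comparison | 86.7% | 92.5% |
| 20%, 20%, 20% | all three | 71% | 86% |
| 20%, 20%, 30% | each arm at 20% | 86.7% | 89% |
| 20%, 20%, 30% | both arms at 20% | 78% | 83% |

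The price appears in the last scenario. In the simulation, the chance of wrongly passing the arm at 30% rises from 1.7% to about 5.0%, which is the family limit. With all three arms at 30%, the chance of any false claim is the same under both rules, about 4.5%.

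**5. The stricter level.** At 0.83% per side, the equal split gives 80.1% per comparison and about 60% for all three; Holm with a 2.5% one-sided family level gives 76% for all three. These figures apply only if the level in use is the one that reproduces 336.

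**The case against.** **Power per comparison is a normal convention.** This stands. The section defines its comparisons as AS3+SP against each other arm and never claims 80% for all three together. A reader might infer that the printed 80% contradicts the aim for three arms. The text does not support that. The protocol elsewhere seeks the most suitable regimen, and that choice does not need all three arms to pass. Splitting the level also points to separate claims. If success meant all three passing, no split would be needed, and testing each at the full 5% would give about 87% at 336 per arm.

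**The hypothesis is a joint statement.** Section V says: "Three doses of artesunate combined with SP or amodiaquine, and Lapdap used alone will be equally as effective at preventing malaria". A reader might take this as support for an all-three requirement. However, its reference is AS1+SP, whereas the sample size section compares against AS3+SP. It concerns a different set of comparisons and cannot be used here. The two sections must be reconciled as a separate matter.

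**A reader might quote 60% as the power for all three.** That figure belongs to 0.83% per side, which the protocol does not state. At the stated one-sided 5/3% the figure is about 71%.

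**Sizing at α/3 does not forbid Holm later.** This stands in part. The analysis section states no testing rule, and an analysis plan that is not shown may use a step-down test. But 5/3% for each comparison is the only rule the protocol gives, and the power of the trial is presented on it.

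**The gain is a best case, and fixed limits are simpler.** Both stand. The 15-point gain for all three needs every arm to equal the comparator, and even then Holm misses at least one arm in about 14% of trials. Simple confidence limits suit a conclusion framed by a margin.

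**Conclusion.** The sample size is not wrong on this account, and the printed 80% is not a false claim. What holds is narrower: the only multiplicity rule in the protocol is less powerful than an available procedure with the same 5% one-sided family error.

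With all arms truly at 20%, Holm adds about 6 points per comparison (86.7% to 92.5%) and about 15 points for all three (71% to 86%). With one arm at 30%, it adds between 2 and 3 points for each of the other two, and about 5 points for both.

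These sizes rest on 336 evaluable children per arm, a 10-point absolute margin, the stated one-sided 5/3% and a Wald test. If all 420 per arm were followed, power for all three would be about 84% with the equal split and 93% with Holm, so the advantage would shrink but remain. That Holm rejects at least as much at the same family error does not depend on any of these assumptions.

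**What to change.** In the sample size section:

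- Keep 420 children per arm and the 5% one-sided family level.
- Test the three one-sided non-inferiority p-values by Holm: the smallest against α/3, the next against α/2, the largest against α.
- Say that the printed power is per comparison, and give beside it the power for all three arms within the margin: about 86% with Holm, against about 71% with a fixed 5/3%, on 336 evaluable per arm and 20% in every arm.
- Repeat the testing rule in section 13.3.

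This costs a few sentences and needs no extra children or data. Confidence limits that correspond exactly to Holm decisions are less simple, so the fixed 5/3% limits should still be reported. The text should say that Holm governs the claim where the two differ.

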**Sample size:**

- 1680 children aged 1 to 6 years (420 for each of the four arms)

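### The significance level is misprinted by a factor of 100, and 336 per arm at 80% power matches 5/3% used two-sided, not one-sided as stated

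*Protocol*

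**What the plan says.** All the inputs are in the Protocol, Section VI, under Sample size calculations.

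- Design: "The trial is powered as an ‘equivalence’ or ‘negative’ trial". The outcome is the proportion of children with at least one malaria episode.
- Comparator rate: AS3+SP is expected to have a cumulative incidence of 20%.
- Ceiling for the other arms: "we aim to show that this is no more than 30% in the other three arms".
- Reason for adjusting the level: "To allow for three comparisons — AS3+SP compared with each of the other three arms".
- Level, power and size: "we set the significance level to 5/3% (≈0.0167%), one-sided. With 80% power, we need 336 children per arm". Allowing for 20% loss to follow-up, this becomes 420 per arm and 1680 in total. The Study Outline gives the same totals.

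This is the only level that the protocol states for these three comparisons. Section 13.3 names protective efficacy, Kaplan-Meier curves and the log-rank test, without a level. The 5% two-sided level in the sample size section belongs to the drug resistance endpoint.

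**The concern.** The sentence gives the level twice, and the two values differ a hundredfold. Removing the misprint does not settle the matter, because the level, its sidedness, the power and the number per arm should determine one another, and with the standard formula they do not.

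At stake is which confidence limit the three comparisons should use. A one-sided 1.67% level goes with an upper one-sided 98.33% limit. A one-sided 0.83% level goes with a two-sided 98.33% interval, whose upper limit is a one-sided 99.17% limit. An analyst who takes the level from this section could defend either: the word one-sided supports the first, and the number 336 at 80% power supports the second. The choice should be fixed before the data are seen.

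**Working it through.** **Inputs (Protocol, Sample size calculations).** Expected incidence on AS3+SP 20%; ceiling 30%, so the margin is 10 percentage points; 80% power; 5% divided over three comparisons; equal allocation. The true rate is taken as 20% in both arms, which is the usual assumption for a trial of this kind and is not spelled out in the text.

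**Unit check.** 5%/3 = 1.667% = 0.01667. The bracket prints 0.0167%, which is 0.000167. The ratio is 100.

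**Formula.** n per arm = (z_α + z_β)² × [0.2×0.8 + 0.2×0.8] / 0.1² = 32 × (z_α + z_β)², with z_β = 0.842 for 80% power.

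**Reproducing the plan's 336.** Split 5/3% over two tails, which leaves 0.833% in the tested tail, so z_α = 2.394. Then 32 × (2.394 + 0.842)² = 335.01 (unrounded z values), rounded up to 336. This matches. The remaining steps also hold: 336/0.8 = 420 and 4 × 420 = 1680.

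**The level as labelled.** With 5/3% one-sided, z_α = 2.128. Then 32 × (2.128 + 0.842)² = 282.2, rounded up to 283. After 20% loss this is 283/0.8 = 353.75, so 354 per arm and 1416 in total. This does not match.

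**Power at 336 evaluable per arm.** The standard error is √(0.32/336) = 0.03086, and 0.1/0.03086 = 3.240.

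| Level in tested tail | z_α | 3.240 − z_α | Power at 336 | n for 80% power |
|---|---|---|---|---|
| 1.67% (5/3% one-sided, as labelled) | 2.128 | 1.112 | 86.7% | 283 |
| 0.83% (5/3% two-sided) | 2.394 | 0.846 | 80.1% | 336 |

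**Effect on a conclusion.** With rates near 20% and 336 per arm, the upper limit stays below 10 points if the observed excess over AS3+SP is less than 10 − 2.128 × 3.086 = 3.4 points at 1.67%, or 10 − 2.394 × 3.086 = 2.6 points at 0.83%. A regimen observed 3 points worse would meet the margin under one level and miss it under the other.

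**Other formulas at one-sided 5/3% and 80% power.** Restricted-variance 286; continuity-corrected 302; two-sided equivalence form, with β split, 373. None gives 336. A superiority formula for 20% against 30% gives 330, which is close, but it does not use the stated design.

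**The case against.** The strongest case on the other side is that this is a typing slip. The protocol shows where the level comes from, 5% over three comparisons, so the intended value is plainly 5/3%, and no calculation in the protocol uses 0.0167%. The size is generous or right on either credible reading. The section also cites a published method that is not available here, and a confidence level may properly be set in an analysis plan that is not shown.

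Most of this stands, and it rules out several stronger readings that a reader might infer:

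- **That 0.0167% is a real candidate level.** Tested at that level, 80% power would need 628 per arm, and 336 would give about 36% power. The stated derivation excludes this, so those figures are not consequences of the plan.
- **That 336 has no basis in the stated inputs.** It follows exactly from 5/3% taken as two-sided.
- **That 336 came from one-sided 2.5% with 90% power and no adjustment.** That calculation gives 336.2, so 337 when rounded up, and it contradicts both the stated 80% power and the stated allowance for three comparisons.

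What the objection does not remove is the second mismatch. With the percent sign corrected, the label one-sided still disagrees with 336 at 80% power, and nothing else in the protocol resolves it. This is a conflict within a sentence that the protocol does state, not a detail left for the analysis plan.

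**Conclusion.** The point holds in a limited form. The bracket is wrong by a factor of 100. Separately, 336 per arm at 80% power is not the result for one-sided 5/3%, which needs 283 and has about 87% power at 336. It is the result for 0.83% in the tested tail, with 80.1% power. What remains open is a twofold difference in the level, 1.67% against 0.83%, not a hundredfold one.

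A reader might infer that the trial is too small or that its power claim fails. The documents do not support that: power is at least 80% on both credible readings.

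The conclusion assumes a true rate of 20% in both arms and the standard unpooled formula. That 5/3% was used two-sided is the best match to the stated figures, but it cannot be confirmed without the cited paper.

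**What to change.** Correct the bracket to 1.67% (0.0167 as a proportion), and make level and power agree in one of two ways:

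1. State a one-sided level of 1.67% for each comparison, that is an upper one-sided 98.33% confidence limit. Restate the power as about 87% with 336 evaluable children per arm, and note that 80% needs 283.
2. State a one-sided level of 0.83% for each comparison, that is a two-sided 98.33% confidence interval. Keep 336 per arm at 80% power.

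The authors should choose the one that they intended, before the data are seen. Either way, 420 per arm and 1680 in total stay unchanged. The cost is one corrected sentence, with no change in enrolment.

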2.3 Intermittent preventive treatment in children (sIPT or IPTc)

The two studies conducted in Tanzania, where malaria transmission is intense and perennial have shown that IPT during infancy has the potential to become a major tool for malaria control in highly endemic parts of Africa. However, in many parts of Africa, especially those where transmission is seasonal, the main burden of malaria is in older children who would not be protected by an IPTi scheme which is limited to infants only. Except for impregnated bednets, there are no other efficacious tools available for preventing malaria in these children. Thus, we have explored the feasibility of using the IPT approach to prevent malaria in older children.

With support from the Gates Malaria Partnership, a study was undertaken in 2002 in children in Niakhar, a typical Soudano-Sahelian area of rural Senegal where malaria transmission is seasonal and intense. A single dose of SP plus one day of artesunate were given to 600 children in September, October and November, whilst 600 other children received a placebo. The incidence of clinical malaria was reduced by 86% in children who received the intervention.

Cross-sectional surveys were undertaken before and after the administration of sIPT. The prevalence of *Plasmodium falciparum* parasitaemia at the end of the malaria transmission season in children who had received the drug combination was 69% less than in the control children (11%% versus 35%). However, molecular studies showed that there had been a selection of parasites with *dhfr* mutations associated with pyrimethamine resistance in the children who had received SP plus artesunate but not in the control group. Although there was no overall increase in the number of resistant parasites in the children who had received sIPT, because the prevalence of infection was markedly reduced in these children, this finding is a matter of concern.

A single dose of artesunate has not been effective in preventing selection for parasites carrying genetic markers of SP resistance. Although the intervention reduces the absolute number of parasites with resistant genes to SP because of the lower carriage of parasites induced, there is significant selection for resistant genotypes in the IPT group. 95% of parasites in IPT recipients carried triple mutations in *pfdhfr* compared to 75% of parasites in the placebo recipients. (figure 1).

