At the time of the cross-sectional surveys filter paper blood samples will be collected and stored at 4 o C prior to analysis of molecular markers for resistance. For those children parasite-positive by microscopy, DNA will be extracted from the filter paper samples using standard techniques and amplified using PCR (Djimde, Doumbo et al. 2001). The reaction products will be probed for defined mutations in the dihydofolate reductase (*dhfr*), dihydroptypteroate (*dhps*) (Peterson, Di Santi et al. 1991) and *pfcrt* genes of *Plasmodium falciparum* using SSOP (Alloueche, Silveira et al. 2000). The prevalence of *dhfr* and *dhps* mutations associated with resistance to pyrimethamine will be compared between pre and post sIPT treatment samples in children who receive SP plus artesunate or Lapdap. Children who receive amodiaquine plus artesunate will act as controls. Similarly changes in the prevalence of *pfcrt* mutations before and after treatment will be measured in children who receive sIPT with amodiaquine plus artesunate whilst samples from children who receive SP or Lapdap will act as controls

1. Assessments of adverse events

Adverse events will be defined as any signs or symptoms, which first develop or increase in severity within seven days after intake. Any serious adverse events such as death or admission to hospital which occur within one week of drug administration will be thoroughly investigated and reported within 24 hours to the DSMB. To determine the prevalence of minor side effects following drug administration such as headache, fever, weakness, abdominal pain, anorexia, nausea, vomiting, diarrhoea, rash, itching or sleep disorder 100 randomly selected participants in each treatment group will be visited at home seven days after each round of drug administration and a side effects questionnaire completed. (*appendix 5*) Field staffs who complete these questionnaires will be unaware of the treatment group to which the child belongs.

1. Participants withdrawal

Parents will be at liberty to withdraw their children from the study at any time for any reason; this decision will not prejudice their children receiving malaria treatment.

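### The 77% power for the resistance endpoint counts clinical malaria cases, but only children slide-positive at the surveys are genotyped; at the protocol's 11% prevalence, power is about 46–57%

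*Protocol*

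**What the plan says.** **The power statement (Section VI.4, Sample size calculations).** The clinical outcome is the proportion of children with at least one malaria episode during the study, expected to be 20% on AS3+SP, with 336 evaluable children per arm (420 randomised, allowing up to 20% loss). The text then turns to resistance: "For the secondary drug resistance endpoint, this implies 336×0.2=67 cases on AS3+SP". The same number is assumed in the other arms. Among these cases, *dhfr* mutation prevalence is expected "to be 90% in the AS1+SP arm", and the conclusion is "The 67 cases per arm then give us 77% power to detect a difference of 20% (ie 70% prevalence) in the other arms". The test is two-sided at 5%, and Fleiss is cited for the method.

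**The sampling plan (Section VI.8, Assessment of resistances).** Filter papers are taken at the cross-sectional surveys, and "For those children parasite-positive by microscopy, DNA will be extracted from the filter paper samples". The Study Outline (Follow-up), Section VI.5 and Section 13.3 also place resistance sampling at the two surveys. Section VI.5 dates them to the first drug round (September) and one month after the last (December).

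**The endpoint (Section V).** It is the prevalence of resistance-associated genotypes after sIPT at the end of the transmission season.

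**The 2002 data.** Section IV.2.3 says that end-of-season parasite prevalence in treated children "was 69% less than in the control children (11%% versus 35" per cent). It gives triple-mutant prevalence as 95% in treated children "compared to 75% of parasites in the placebo recipients". Section 13.3 describes the same study as a rise from around 50% to 90% in the AS1+SP group, and assumes a rise of no more than 50% to 70% on AS3+SP.

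**The concern.** The children counted for power are not the children who will be genotyped. Clinical cases accumulate from September onwards and are treated when found (Section VI.7), so a case contributes a December isolate only if that child is parasite-positive again at the survey. No section provides for filter-paper sampling or genotyping of clinical cases. The denominator of the resistance comparison is therefore set by parasite prevalence at the December survey. The protocol's own figure for that after sIPT is little more than half of the 20% used.

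Resistance selection is the reason given for testing new regimens. Section V makes it one of two major endpoints, and Section 13.3 says the sample size was worked out particularly for it. An overstated power for this comparison bears on what the trial can say about its main question.

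**Working it through.** **Inputs**
- Two-sided 5%, Fleiss formula; 90% (AS1+SP) versus 70% (other arms), so d = 0.20: Section VI.4.
- 336 evaluable and 420 randomised per arm: Section VI.4.
- End-of-season parasite prevalence 11% after SP plus one day of artesunate, 35% in controls: Section IV.2.3.
- *Assumption:* 11% applies in all four arms. The protocol gives no survey prevalence for the other regimens.

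**Formula.** For n isolates per arm, the continuity correction reduces n to an effective size:

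n_eff = n − 2/d + 1/(n·d²)

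Power = Φ{ [d·√n_eff − 1.96·√(2·p̄·(1−p̄))] / √[p₁(1−p₁) + p₂(1−p₂)] }, where p̄ = 0.80.

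For 90% versus 70%, the term subtracted in the numerator is 1.96 × √0.32 = 1.109, and the denominator is √0.30 = 0.548.

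**Step 1: reproduce the stated figure.** n = 67: n_eff = 67 − 10 + 25/67 = 57.37. Then 0.2 × √57.37 = 1.515, z = (1.515 − 1.109)/0.548 = 0.74, power **77.1%**. This matches the protocol's 77%, so this is the protocol's method.

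**Step 2: count the children who will be genotyped.**
- 336 × 0.11 = 36.96, about **37** per arm.
- With no loss, 420 × 0.11 = 46.2, about **46** per arm.
- To reach 67 would need 67/336 = 20% survey prevalence (67/420 = 16% with no loss).

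**Step 3: power with those numbers, 90% versus 70%.**
- n = 37: n_eff = 37 − 10 + 25/37 = 27.68; z = (1.052 − 1.109)/0.548 = −0.10; power **45.9%**.
- n = 46: n_eff = 36.54; z = (1.209 − 1.109)/0.548 = 0.18; power **57.3%**.
- n = 30 to 50 (survey prevalence of about 9% to 15% among 336): **36% to 62%**.

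**Step 4: unequal numbers of isolates.** Suppose AS1+SP has 37 isolates and the comparison arm has r times as many. The effective size becomes n − (r+1)/(r·d) + [(r+1)/(r·d)]²/(4n), and the variance terms are adjusted for the ratio.
- r = 2: n_eff = 37 − 7.5 + 56.25/148 = 29.88; power **57%**.
- r = 3: n_eff = 37 − 6.67 + 44.4/148 = 30.63; power **62%**.

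At r = 3 the comparison arm has 3 × 11% = 33% prevalence, close to the 35% in untreated children in 2002.

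**Step 5: other formulas, 90% versus 70%.** Without continuity correction, n = 37 gives 57.8% and n = 46 gives 67.5%, against 83.3% at n = 67. Fisher's exact test gives 48.8% at n = 37, against 79.2% at n = 67. The loss is of similar size whichever method is used.

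**Step 6: the Section IV.2.3 mutation figures.** For 95% versus 75%, the continuity-corrected formula gives 55% at n = 37 and 67% at n = 46, against 86% at n = 67.

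**The case against.** **The 11% is one arm in one season.** This stands. It comes from AS1+SP in 2002, and prevalence under AS3+SP, artesunate plus amodiaquine and Lapdap is not given anywhere. Section VI.4 also notes that less effective arms would add power. But AS1+SP is one side of the stated comparison, so its small count limits power; even a threefold count in the other arm gives only 62%. A reader might take 46% as the trial's actual power. It is the value under full 20% loss and 11% everywhere, and the protocol expects no more than 20% loss.

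**The 90% and 70% are not unexplained.** This also stands: Section 13.3 gives their origin. A reader might infer that a 70% target is incoherent because it lies below the 75% seen in untreated children. That accepts Section IV.2.3 over Section 13.3, which starts from about 50%. The figure showing prevalence before and after by group is not available, so the documents do not settle which account is right. On its own, the Section IV.2.3 pair would raise power, not lower it. With that pair, no loss and no continuity correction, power would be about 78%; this takes three favourable departures from Section VI.4's calculation, and the like-for-like figure at 67 would be 91%.

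**Resistance is labelled secondary in Section VI.4.** That is so, but Sections V and 13.3 give it major status.

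**Nothing says that a null result will be read as equal selection.** Correct. The hypothesis in Section V is that the alternatives select less; equivalence is claimed for efficacy only. The risk of misreading is a reason for careful reporting, not a stated error in the plan.

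**Conclusion.** The concern holds as an inconsistency in the sampling unit. The protocol's arithmetic is correct for 67 isolates, but its sampling plan does not produce 67 unless about 20% of evaluable children are slide-positive in December. At the protocol's only relevant figure, 11%, the stated 77% falls to about 46% with the planned loss and 57% with none, for 90% versus 70%. It stays at 57–62% if the comparison arm has two to three times AS1+SP's 37 isolates. The exact value depends on a prevalence not known for three of the four arms; the direction does not change in any like-for-like variant examined. Separately, Sections IV.2.3 and 13.3 report the 2002 mutation results differently and must be reconciled. The documents do not show which is right, nor that the 70% target is wrong.

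**What to change.** 1. In Section VI.4, replace the 67-case calculation with the expected number of slide-positive children at the December survey: 336 × 11% ≈ 37 per arm, 46 with no loss. State that applying 11% to all arms is an assumption.
2. Restate power as about 46–57% for 90% versus 70%, or 36–62% if a range of 30–50 isolates per arm is given.
3. Reconcile the 2002 mutation figures in Sections IV.2.3 and 13.3, and carry one set through. If 95% versus 75% is adopted, power is about 55–67% at 37–46 isolates.
4. Report the between-arm difference in mutation prevalence with its confidence interval, and say that a non-significant result is not evidence of equal selection.

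The cost is revised text in Sections IV.2.3, VI.4 and 13.3 and a less favourable power statement, with no extra children or samples. If genotyping of clinical cases was in fact intended, the sampling plan and the endpoint definition would have to be changed to say so. That would add samples and change what the endpoint measures.
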